#### Qualitative survey tool development

The tool being utilized for the qualitative assessment is developed on the basis of the intervention programming itself. A key informant interview guide has been prepared for the MEAL coordinator, the Nutrition Manager, and the Nutrition Officer (Program staff) while focus group discussion guides have been developed for the NIPP and NIPP+ volunteer and the circle participants. Qualitative data will be collected at endline with the MEAL coordinator, the Nutrition Program Officer, and 10 Nutrition Officers who work directly on the implementation of the NIPP and NIPP+ activities using semi-structured questionnaires. Interviews will also be conducted with 10 NIPP and 10 NIPP+ volunteers. Focus group discussions will be carried out with a maximum of 40 female participants (20 in NIPP and 20 in NIPP+ female circle) and 40 male participants (20 in NIPP and 20 NIPP+ circles). We anticipate each focus group to be composed of not more than 10 participants which will allow us to have 4 focus groups for women and 4 for men (2 in each intervention arm).

### Data management and statistical analysis

#### Data entry and management

To maintain a high level of data quality, the research team will use Digital Data Gathering (DDG) tools (which have become common in this field). The DDG reduces the number of man-made mistakes in the survey by providing a clear and easy-to-use platform for inputting data. In addition, almost real-time access (uploaded once Internet is available) to the data will allow a research to look for common mistakes (such as bundling of child age by 12, 24, 36, etc. months) and providing additional input/advice to the enumerators to eliminate those mistakes while still in the field. Once the data is collected, we will also look at whether certain responses are correlated to certain enumerators to make sure that the data was collected similarly across all enumerators. For the anthropometry data, values more than five standard deviations above and below the median WHO standards will be removed [3]. The final de-identified data will be shared via the Development Experience Clearinghouse (DEC).

#### Statistical methods for assessing impact

For the analysis, we will use an intent-to-treat (ITT) approach using the initial randomization of the treatment arms. While we know that there could be some contamination across groups or non-adherence, we will plan for the clusters to be sufficiently far apart that this should limit any bias related to self-selection captured via retention or adherence. Using ITT will allow us to determine the overall impact of having the NIPP vs. NIPP+ vs. control in your community, thus better mimicking real-world program implementation and impact. Each survey question will have the option of “Refused to Answer” or “Don’t Know” and will eventually be transformed into missing variables. Prior to that transformation, we will use the proportion of RA or DK responses to understand the sensitivity of the question itself. We will use the standard rule where if fewer than 5% of your observations are missing, the variable will remain in the analysis. If the 5% or more of observations are missing, we will not use the variable to avoid drawing inaccurate inferences. We will not impute missing data.

For the analysis, we will take advantage of the panel to run mixed effects models, allowing us to determine the role of time-variant and invariant individual household, and community characteristics, as well as measures of exposure and integration on key outcome indicators (Table 1 above). In addition, we will use a difference-in-difference analysis (baseline/endline, baseline/sustainability, endline/sustainability) to triangulate findings. To complement these models, the analysis will also leverage exploratory analysis to identify cross-cutting or underlying correlations using principal component analysis. For all of the analysis, we will control for a host of individual-, household-, and community-level characteristics.

The specific models run will depend on the distribution of our key outcome variables. Most of our variables are continuous and therefore we will use either an ordinary least squares, Poisson, or negative binomial regression (depending on the distribution of the variable) to compare across the three treatment arms. For binary variables (such as whether the household reported using improved seeds), we will use a logit model. All analysis will control for the complex survey design. For each key outcome variable, we will run a crude model (meaning only looking at the relationship between the outcome variable and intervention) and an adjusted model (controlling for key household and child demographics such as gender, age, education, and household size). A comprehensive research uptake strategy will be developed alongside stakeholders in Uganda.

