**Intervention:**

Compare the Nutrition Impact and Positive Practice (NIPP) approach to a NIPP+ approach. The NIPP approach involves nutrition education and SBC, whereas the NIPP+ adds agricultural inputs, training, and tools to support improved farm and water quality practices. The intervention effect will be measured through lower levels of aflatoxin in grain, lower water contamination, and improved knowledge on nutrition and health.

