**Water quality**		
Reported knowledge of water quality assessment	Baseline, endline, 2- and 6-month follow-up sustainability	Quantitative
Reported purchase of water tests	Endline, 2- and 6-month follow-up, sustainability	Quantitative
Reported use of water tests	Endline, 2- and 6-month follow-up, sustainability	Quantitative

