**Use of improved varieties and fertilizer**		
Reported purchase of improved maize varieties	Baseline, endline, and sustainability	Quantitative
Reported planting of improved maize varieties	Baseline, endline, and sustainability	Quantitative
Reported knowledge of vendors for improved varieties	Baseline, endline, and sustainability	Quantitative
# of interactions with vendors	Baseline, endline, and sustainability	Quantitative
Reported knowledge of fertilizer availability	Baseline, endline, and sustainability	Quantitative
Reported use of fertilizer	Baseline, endline, and sustainability	Quantitative
Reported use of improved seed varieties for the planting season after the intervention	Endline, 2- and 6-month follow-up, and sustainability	Quantitative

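### Don't Know is recoded to missing on every survey question with no exception for knowledge items, so valid answers meaning no knowledge can remove an item or distort its arm contrast

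*Protocol article*

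**What the plan says.** The rule is in the protocol article under 'Statistical methods for assessing impact'. Its scope is universal: "Each survey question will have the option of" Refused to Answer or Don't Know. Both codes are treated alike, "and will eventually be transformed into missing variables. Prior to that transformation, we will use the proportion of RA or DK responses", and that prior use is diagnostic only, to gauge how sensitive the question is. The retention rule follows: "if fewer than 5% of your observations are missing, the variable will remain in the analysis". At 5% or more the variable is not used. Missing data are not imputed.

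Elsewhere the article treats knowledge as something the trial measures:

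- The abstract says that the intervention effect will be measured through "lower levels of aflatoxin in grain, lower water contamination, and improved knowledge on nutrition and health".
- Aim 3 covers sustained impact on knowledge as well as practices.
- The household survey has a component on knowledge of health behaviours, and the agriculture survey one on knowledge of good agronomic practices.
- Table 4 lists, among others, "Reported knowledge of water quality assessment" and "Reported knowledge of vendors for improved varieties". It also has knowledge items on moisture assessment, improved storage and fertilizer availability. All are scheduled at baseline, endline and sustainability.

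No section says that DK on a knowledge item is scored as not knowing.

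**The concern.** On a question about income or last season's yield, DK is item non-response, and coding it as missing is ordinary practice. On a question that tests whether the respondent knows something, DK is the result. Setting it to missing removes the least informed respondents from the denominator and changes the measure from correct/all to correct/(correct + wrong).

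Two things are at stake. First, the 5% rule can discard a knowledge item even when follow-up is complete. The items most exposed are those on which ignorance is common at baseline, which are the ones with most room to improve. Second, an item that survives is analysed in a set of respondents selected on the outcome after randomization. This sits badly with the intent-to-treat aim in the same section, and it distorts the arm contrast whenever the DK and correct shares differ between arms in the wrong combination.

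**Working it through.** **Inputs from the article.** 900 households, 300 per arm; variables dropped at 5% or more missing; DK and refusals both set to missing; no imputation. The article gives no shares correct or DK and no figure of its own to reproduce, so the shares below are assumptions.

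**Step 1: what reaches the cut.**

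- Counted per round over all arms: 0.05 × 900 = 45 DK answers.
- Counted within an arm: 0.05 × 300 = 15.
- Counted over the three full rounds together: 0.05 × 2,700 = 135.

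The article does not say which count applies.

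**Step 2: effect on an item.** Let c be the share correct and d the share DK in an arm, with 0 for control and 1 for intervention.

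- DK scored as not knowing: difference = c1 − c0.
- DK set to missing: difference = c1/(1 − d1) − c0/(1 − d0).
- Since c/(1 − d) = c + c·d/(1 − d), recoding adds c·d/(1 − d) to each arm's figure. The contrast shrinks only if this addition is larger in control than in the intervention arm.

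**Step 3: numbers (assumed shares, control vs one intervention arm).** 'Kept' and 'dropped' use DK averaged over the two arms.

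| Correct | DK | Mean DK | True difference | After recoding | 5% rule |
|---|---|---|---|---|---|
| 50% vs 58% | 8% vs 1% | 4.5% | 8.0 | 58.6 − 54.3 = 4.2 | kept |
| 60% vs 70% | 8% vs 1% | 4.5% | 10.0 | 70.7 − 65.2 = 5.5 | kept |
| 50% vs 60% | 4% vs 4% | 4.0% | 10.0 | 62.5 − 52.1 = 10.4 | kept |
| 50% vs 60% | 1% vs 8% | 4.5% | 10.0 | 65.2 − 50.5 = 14.7 | kept |
| 50% vs 70% | 30% vs 10% | 20% | 20.0 | 77.8 − 71.4 = 6.3 | dropped |
| 5% vs 50% | 40% vs 20% | 30% | 45.0 | 62.5 − 8.3 = 54.2 | dropped |

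Differences are in percentage points, computed before rounding.

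**Step 4: check of the first row against all three arms.** DK of 8% and 1% is 24 + 3 = 27 answers. The item stays under 45 if the third arm has fewer than 18 DK answers (6% of 300). If the cut applied within each arm, 24 answers in control would already exceed 15 and the item would go.

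**Reading.** The first two rows show the expected pattern, in which the intervention turns DK into answers: roughly half the difference is lost. The third row shows almost no change. The fourth shows inflation when DK rises in the intervention arm. The last shows that the contrast can be inflated even when DK is commoner in control, because the control addition (0.05 × 0.40/0.60 = 3.3 points) is smaller than the intervention addition (0.50 × 0.20/0.80 = 12.5 points). The last two rows would never be reported, because the 5% rule removes the item first.

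**The case against.** Four objections carry weight.

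- **Direction.** A reader might infer that the recode always biases the knowledge effect toward zero. The arithmetic does not support that: the result depends on the share correct as well as the share DK, and the contrast can shrink, hold or grow. This objection stands in full.
- **Size.** A reader might also point to very large losses, such as 20 points read as 6.3. Those need DK levels well above 5%, at which the plan would not analyse the item. Distortion is confined to items below the cut; above it, the harm is loss of the item. This also stands.
- **Item format.** The questionnaire is not shown. The Table 4 items are reported knowledge. If they are yes/no questions, a respondent without the knowledge may answer No and stay in the denominator. How often DK carries the meaning of no knowledge therefore cannot be established. This limits the reach of the point, but the rule remains wrong for any item on which DK does mean that.
- **Weight.** Table 3 lists no knowledge measure as a primary or secondary outcome, Table 4 is a monitoring and sustainability table, and the sample size does not rest on knowledge. This stands and bounds the severity.

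A fifth objection, that item scoring is commonly left to a codebook or analysis plan, is weaker. The article is not silent here. It fixes a rule for every survey question, and that rule gives the wrong result on knowledge items.

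**Conclusion.** The point holds in a limited form. As written, the plan sets DK to missing on knowledge items as on all others, and discards the item at 5% missing. The more likely harm is loss of the item, at 45 DK answers among 900 households if the cut is counted per round over all arms. For an item that survives, the arm contrast is distorted. Under the assumed shares that fit an intervention reducing DK, true differences of 8.0 and 10.0 points become 4.2 and 5.5; under other shares the contrast is nearly unchanged or inflated. No general claim of bias toward no effect is justified.

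The conclusion rests on there being items where DK means no knowledge, and on assumed response shares. The harm falls on the abstract's knowledge measure, Aim 3 and the Table 4 knowledge items. The primary and secondary outcomes in Table 3 are not touched by this point. It should be corrected, but it does not threaten the trial's main conclusions.

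**What to change.** Add one sentence to 'Statistical methods for assessing impact': on knowledge and awareness items in the household survey, the agriculture survey and Table 4, DK is scored as not knowing, the respondent stays in the denominator, and these answers do not count toward the 5% rule. Refused to Answer stays missing on all items, and DK stays missing on factual recall items. List the items treated as knowledge items, and fix the list before outcome data are examined by arm.

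The cost is one sentence and a recode in data cleaning. The DK answers are already collected, so no new data are needed.

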### Sample size calculation and sampling strategy

To detect meaningful differences in the change in the primary outcome measures across the three arms with a power of 0.80, a significance level of 0.05, and an intra-class correlation of 0.05, each treatment arm will require 17 clusters with 15 households (with children under the age of 2) in each cluster (Table 2). We used secondary data on all outcome measures (except total coliform) from Northern Uganda and collected as part of the Feed the Future Innovation Lab for Nutrition Uganda Birth Cohort Study [24]. We aim to follow the same households throughout the duration of the study. Thus, the sample size is adjusted for 20% attrition. This increase will come from additional clusters and not households (to keep the integrity of the NIPP 15 households/circle programmatic design). The sample will include 20 clusters per arm for a total of 60 clusters and 15 households per cluster with an overall household sample size of 900. Based on the results of cluster randomization, trained study personnel will approach households that meet the study’s inclusion criteria in the parishes selected for the study. They will approach eligible households and seek consent until a total of 15 households agree thus forming a cluster. The sampling at the household level is purposeful. A random subsample of households will be taken at 2 months and interviewed again at 6 months post-intervention. This sample size is a fixed sample of 82 households per intervention arm.

**Table 2 Tab2:** Sample size calculation for quantitative evaluation

Category	Mean	*SD*	ICC^a^	Effect size (Cohn’s)	Sample size/treatment arm	Total sample size
*E. coli*	31.56	45.14	0.05	0.67	120 (20 clusters*5 hh per cluster + 20% for attrition)	≈ 360
Aflatoxin	20	43.6	0.05	0.34	306 (17 clusters*15 hh per cluster + 20% for attrition)	≈ 900

^a^The ICC calculated for aflatoxin for mothers was close to 0 but came from a small sample size. Thus, we have decided to overestimate the ICC to 0.05

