#### Water sample collection for assessing *E. coli* and total coliforms

Microbiological water samples taken from the home and community will be processed within 6 h of sample collection using a membrane filtration method containing m-ColiBlue24 media (Hach Company, Loveland, CO). This method allows for the simultaneous analysis of *E. coli* and total coliforms. We will request each household to provide a 250-ml water sample from the storage container that is used for drinking purposes. At the community level, we will identify the common water sources and request the participants to provide a sample of 250 ml from each common water source. If households within a circle are using different water sources, we will collect a sample from each of the water sources used by the circle participants. For both household and community assessments, the sample will be transferred from a storage container to a sterile plastic bottle, placed into a cooler, and transported back to a makeshift lab where the water will be analyzed for *E. coli* and total coliforms. As we will only need 360 household samples per data collection (baseline, endline, sustainability), we will randomly select these households in advance in such a way that we are collecting 6 samples per every cluster (60 clusters × 6 samples = 360 samples). The same 360 households will be sampled at each time point. The community samples will be collected from every cluster.

At the lab, all water samples will undergo the following process: dilution with sterile buffered water, vacuum-filtered aseptically through 45-μm filters (EMD Millipore, Billerica, MA), placed in plastic Petri dishes with media-soaked pads, and incubated for 24 h at 35 °C. Two dilution volumes will be processed per water sample. As a standard quality control process, 10% of samples will be duplicated and 5% of samples will be blank/control. After incubation, colonies of bacteria will be counted, and concentrations calculated using the geometric mean of plate counts within a countable range (1–250 colonies). Plates with counts < 1 will be assigned 0.5 and > 250 were assigned 250.

As summarized in Table 4, the agriculture survey will be composed of 6 modules that capture information on crop diversity, agriculture inputs, crop yields and production, agriculture practices, and knowledge of GAP. In addition to capturing information through the survey, there will also be samples taken of harvested maize using the following method.

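### The 5% missing-data exclusion rule does not exempt outcomes or define its denominator, so it could remove primary outcomes from a trial sized for 20% attrition

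*Protocol article*

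**What the plan says.** Under Statistical methods for assessing impact, the protocol article explains that Refused and Don't Know answers to survey questions "will eventually be transformed into missing variables". It then sets a two-sided rule. On one side, "if fewer than 5% of your observations are missing, the variable will remain in the analysis". On the other, "If the 5% or more of observations are missing, we will not use the variable to avoid drawing inaccurate inferences". The paragraph ends: "We will not impute missing data". It does not separate outcomes from covariates. It also does not say whether the percentage is taken per round, over all rounds, or among interviewed households only.

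Under Sample size calculation and sampling strategy, the design is a panel: "We aim to follow the same households throughout the duration of the study". The next sentence reads: "Thus, the sample size is adjusted for 20% attrition". Table 2 applies that allowance to both outcomes that it sizes, E. coli and aflatoxin.

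Table 3 lists women's and child dietary diversity, E. coli, aflatoxin and household food security as primary outcomes, all needed at endline and at the 12-month sustainability round. The difference-in-difference analysis uses those rounds.

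**The concern.** A trial that allows for one household in five to be lost should have an analysis rule that can live with that loss. The stated rule tolerates less than one in twenty and, as worded, applies to any variable, including a primary outcome.

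Dropping an outcome because some values are missing does not correct the bias that the missing values may cause. It discards the randomised comparison for that outcome. It also makes the set of analysed primary outcomes depend on the data as they come in, when that set should be fixed in advance. Outcomes with the most difficult follow-up would be the first to go, although the sample was enlarged to keep them informative.

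**Working it through.** **Inputs.** 900 households, 60 clusters, 20 clusters per arm, 15 households per cluster, 20% attrition, standardised effect 0.34 for aflatoxin (Sample size section and Table 2). The section sets the calculation "with a power of 0.80, a significance level of 0.05, and an intra-class correlation of 0.05"; a two-sided test is assumed. The 5% cut-off is from Statistical methods for assessing impact. The E. coli sub-sample comes from the water sampling section: "As we will only need 360 household samples per data collection", with the same households sampled each round.

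**The plan's own figure.** For d = 0.34, the unclustered size is 136 per arm. The design effect is 1 + (15 − 1) × 0.05 = 1.70, and 136 × 1.70 = 231.2, which is 15.4 clusters. With a t test on 2(k − 1) degrees of freedom, 16 clusters per arm give power 0.789 and 17 give 0.815, so the stated 17 is reproduced. Then 17 × 15 = 255 and 255 × 1.2 = 306, as in Table 2. For E. coli, 20 × 5 × 1.2 = 120 per arm, or 360 in total. The 20% allowance is therefore built into both sizes.

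**Reading A: lost households count as missing observations.**

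| Outcome base | Cut-off (5%) | Planned loss (20%) | Ratio |
|---|---|---|---|
| All households | 0.05 × 900 = 45 | 0.20 × 900 = 180 | 4 |
| E. coli sub-sample | 0.05 × 360 = 18 | 0.20 × 360 = 72 | 4 |

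The timing of loss is not stated, so the share pooled over baseline, endline and sustainability is shown as a range:

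- all loss in the last round: 0.20 / 3 = 6.7%
- loss of 0, 10 and 20%: 0.30 / 3 = 10%
- 20% lost at both follow-ups: 0.40 / 3 = 13.3%

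Grain aflatoxin has two rounds, so its share is 0.20 / 2 = 10% to 0.40 / 2 = 20%. Every figure is above 5%. The most lenient case, pooling three rounds with all loss in the last, reaches the cut-off at 0.05 × 3 = 15% attrition.

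**How sharply the rule acts.** The chance that the count of missing households reaches the cut-off, from a binomial that treats households as independent:

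| True missing share | N = 900 | N = 360 |
|---|---|---|
| 4% | 0.08 | 0.20 |
| 5% | 0.52 | 0.53 |
| 6% | 0.91 | 0.82 |
| 20% | 1.00 | 1.00 |

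**Reading B: only Refused and Don't Know answers count, among interviewed households.** Attrition then contributes 0%. The dietary and food-security primary outcomes come from the household survey, so the rule still discards any of them once 5% of answers are missing. The article gives no expected item non-response, so the chance of this cannot be sized.

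**What would be thrown away.** At 80% retention, 20 clusters × 12 households = 240 per arm. With design effect 1 + 11 × 0.05 = 1.55, power for d = 0.34 is about 0.83. The retained data would still meet the trial's own target of 0.80.

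**The case against.** The strongest counter-argument is one of context. The rule follows directly on sentences about survey questions and their Refused and Don't Know options, so it may be meant as a screen for item non-response. Attrition is handled elsewhere by adding clusters, and the next paragraph uses the panel in mixed models. This reading is plausible and stands as one of two. It does not settle the matter: the text does not limit the rule to it, and even then survey-based primary outcomes are not protected. It is also fair that 20% is a planning allowance attached to no particular visit, not an expected or observed loss.

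Several stronger inferences are tempting, but the article does not support them:

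- **E. coli fails by design because 540 of 900 households are never tested.** Those households are not scheduled for sampling, so they are not missing. The right base is 360.
- **Child anthropometry fails because infants are below the age range of the z-scores.** These children are ineligible for the measure, not missing, and anthropometry is a secondary outcome.
- **Adherence would decide which outcomes survive.** Participants who leave the programme are still to be surveyed, and nothing links adherence to item refusal.
- **Empty grain stores would push aflatoxin over the limit.** Collection is timed to follow harvest, and no figure for households without maize is given.
- **The rule contradicts intent-to-treat.** The article uses that term for analysis by the arm assigned at randomisation. Omitting an outcome moves no household between arms; the problem is data-driven selection of outcomes.

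The analysis plan is not shown and may hold further detail on sensitivity analyses, so their absence from the article is not a fault. The exclusion rule is stated in the article and can be judged as it stands.

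**Conclusion.** The concern holds in conditional form. The article states a fixed exclusion rule with undefined scope and denominator and no exemption for outcomes. If lost households count as missing, the attrition that the trial was sized for exceeds the cut-off fourfold within a follow-up round, and by a factor of 1.3 to 2.7 when pooled over three rounds (6.7% to 13.3% against 5%). Follow-up primary outcomes would then be dropped. If only Refused and Don't Know answers count, attrition is harmless, but survey-based primary outcomes remain exposed at 5% item non-response, with a likelihood that cannot be given.

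A reader might infer that the rule will certainly remove primary outcomes. That goes too far, because it depends on the first reading and on loss near the planning allowance. What does not depend on the reading is that observed missingness, and not the protocol, would decide which primary outcomes are analysed. Because primary outcomes are at stake, the text should be corrected before outcome data are seen.

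**What to change.** Amend Statistical methods for assessing impact as follows:

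1. State that the 5% exclusion rule does not apply to primary or secondary outcomes. If it is kept for other variables, define what counts as missing and the denominator.
2. Analyse all available outcome data by randomised arm in the mixed models already planned, taking the sampled households as the denominator for sub-sampled outcomes such as E. coli.
3. Report missingness by arm and round, and do not use it to select outcomes.
4. Add a sensitivity analysis for attrition, with the method left to the analysis plan. If that method involves imputation, restrict the no-imputation sentence to the main analysis.

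The cost is a few sentences and a little more analysis, with no new data. The drawback is that the main analysis relies on a missing-at-random assumption, which the sensitivity analysis is there to probe.
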